#### Outcomes

1.4.4

Outcomes will be assessed during individual appointments at baseline, 8 weeks, 16 weeks and 24 weeks by a research assistant blinded to group allocation. At baseline, demographic and clinical details will be recorded, including age, sex, location of onset of symptoms, time of diagnosis, treatment details and social history. Survival data will be collected after 2 years post study recruitment.

Treatment efficacy will be determined by changes in decline rate of the primary outcomes (Maximal Inspiratory Pressure [MIP], Maximal Expiratory Pressure [MEP], Peak Cough Flow [PCF], Forced Vital Capacity [FVC) and Slow Vital Capacity [SVC]) from baseline to 24 weeks.

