##### Secondary outcomes

1.4.4.4

Data on blood gases will be collected to assess PaCO_2_ levels at baseline. The Amyotrophic Lateral Sclerosis Functional Rating Scale revised score (ALSFR-r), site of onset [bulbar(B) versus non-bulbar (NB)], time elapsed (months) between symptom onset and ALS diagnosis, months elapsed from diagnosis to noninvasive ventilation (NIV) prescription will also be collected. Voice parameters will be assessed by Maximum Phonation Time and its acoustic analysis.

The Functional Oral Intake Scale (FOIS) [19] will be used as an index of daily oral intake. This validated 7-point ordinal scale measures what foods an individual consumes to meet their daily nutritional and hydration requirements and ranges from a 1 (nothing by mouth) to 7 (full oral diet with no restrictions). The Eating Assessment Tool-10 (EAT-10)was administered as a patient reported outcome (PRO) of swallowing function [20]. The EAT-10 is a validated 10-item patient rated questionnaire with each question rated on a 5-point ordinal scale. A total EAT-10 score ranges from 0 (indicative of no self-perceived swallowing impairments) to 40 (indicative of severe swallowing impairments).

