### Sample size calculation

1.5

This study is powered to detect a clinical meaningful difference in decline rate of pulmonary function (% predicted FVC). Based on meta-analysis conducted by Silva et al. [21], the minimal clinical important difference (MCID) from baseline to 1 year is 2–6%, 16 participants for each arm will need to be recruited with 80% power at two-tailed 5% level of significance. After take into account 30% attrition, a total sample size of 42 participants is required.

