### Statistical analysis

1.6

Baseline characteristics will be summarized, including age, sex, time of diagnosis, onset of symptoms local, drugs, primary and secondary outcomes, and imbalances will be investigated.

For each variable, the Shapiro Wilk test will be used to evaluate the normality of the distribution and the Levene test will be performed to evaluate the homogeneity of variance. The differences between groups will be analyzed by the unpaired *t*-test and for continuous variables and chi-square test for categorical variables. The decline rate will be calculated as the difference between baseline and final observation, dividing the result by the number of months between baseline and last evaluation. Spearman test will be used to evaluate the longitudinal decline correlations between pulmonary function tests and both bulbar impairment and disease progression rate.

Exploratory analysis of 2-year survival will include descriptive Kaplan-Mayer survival curves and cox regression with treatment intent.

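### A pre-randomisation disease progression rate can be derived from planned data, but section 1.6 leaves it out of the unadjusted comparison of decline rates: a modest, cheap gain in precision is forgone

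*Protocol article*

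**What the plan says.** Section 1.6 (Statistical analysis) sets the treatment comparison: an unpaired t-test for continuous variables. The decline rate is the change from baseline to the final observation divided by the months between them. No covariate is named. The section also says that baseline imbalances will be looked into, but not what would follow for the comparison of arms.

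Disease progression rate occurs once, in a Spearman analysis of "longitudinal decline correlations between pulmonary function tests and both bulbar impairment and disease progression rate". The article does not say how that rate is computed or whether it is measured before or after randomisation.

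The ingredients of a baseline rate are planned. Section 1.4.4.4 (Secondary outcomes) collects the ALSFRS-R and the "time elapsed (months) between symptom onset and ALS diagnosis". Section 1.4.4 (Outcomes) records "location of onset of symptoms, time of diagnosis" at baseline and schedules outcome assessments at baseline. Section 1.3 stratifies randomisation on bulbar status only.

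**The concern.** The primary endpoints are rates of decline, and the plan itself asks whether decline in lung function tracks disease progression rate. If a patient's speed of disease before entry predicts the speed of decline on study, an unadjusted test carries that variation as noise. Eligibility in section 1.2 sets no limit on speed of progression, so fast and slow progressors may both enter, and stratifying on bulbar status does not directly balance speed. With about 15 to 21 patients per arm analysed, precision is scarce.

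The timing gap matters as well. A progression rate measured during follow-up could be changed by the intervention and would be unsuitable as a covariate. The present wording does not separate the two.

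**Working it through.** **1. The plan's own figure.** Section 1.5 states that "16 participants for each arm will need to be recruited" for "80% power at two-tailed 5% level of significance". The target difference is a range ("the minimal clinical important difference (MCID) from baseline to 1 year is 2–6"%) and no SD is given, so 16 per arm cannot be reproduced forwards. Solved backwards with the t distribution, 16 per arm at 80% power implies a standardised difference d = 1.02 (SD about 2.0 if the difference is 2, about 5.9 if it is 6). I take d = 1.0237 as the base case.

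**2. Patients analysed.** The planned total is 42, or 21 per arm. A 30% loss leaves 42 × 0.70 = 29.4, about 15 per arm. Data before withdrawal are kept (section 1.2) and the rate runs to the last evaluation (section 1.6), so a patient with one post-baseline visit contributes. The number analysed therefore lies between about 15 and 21 per arm.

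**3. Unadjusted power.** Noncentrality = d × √(n/2), with 2n − 2 degrees of freedom. At n = 16: 1.0237 × √8 = 2.895, critical t = 2.042, power 80.0%.

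**4. Power with one baseline covariate.** Let r be the within-arm correlation between the baseline progression rate and the decline rate. Residual variance is multiplied by 1 − r². Estimating the slope costs one degree of freedom (2n − 3) and, on average, a variance factor of 1 + 1/(2n − 4), which is 1.036 at n = 16.

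Noncentrality = d × √(n/2) / √[(1 − r²)(1 + 1/(2n − 4))]

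- r = 0.3, n = 16: 2.895 / √(0.91 × 1.036) = 2.98, critical t = 2.045, power 82.2%.
- r = 0.5, n = 16: 2.895 / √(0.75 × 1.036) = 3.29, power 88.8%.

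**5. Results over an assumed range of r, with d held at 1.02.**

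| Model | Residual variance removed | 15 per arm | 16 per arm | 21 per arm |
|---|---|---|---|---|
| t-test | – | 77.2% | 80.0% | 89.9% |
| adjusted, r = 0 | 0% | 75.6% | 78.5% | 89.1% |
| adjusted, r = 0.2 | 4% | 77.2% | 80.1% | 90.3% |
| adjusted, r = 0.3 | 9% | 79.4% | 82.2% | 91.7% |
| adjusted, r = 0.4 | 16% | 82.5% | 85.1% | 93.6% |
| adjusted, r = 0.5 | 25% | 86.5% | 88.8% | 95.8% |

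Break-even is near r = 0.2. At 16 per arm the gain is about 2 points at r = 0.3, 5 at 0.4 and 9 at 0.5. At 21 per arm it is under 2 points at r = 0.3 and about 6 at r = 0.5.

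**6. Can the covariate be computed?** Months from onset to baseline = months from onset to diagnosis + months from diagnosis to baseline. The first term is collected directly and the second follows from the recorded time of diagnosis. Points lost = maximum ALSFRS-R score − baseline score. This needs the ALSFRS-R at baseline, which the assessment schedule in section 1.4.4 supports.

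**The case against.** The strongest reply is that nothing here is wrong. An unadjusted comparison in a 1:1 randomised trial is valid, and choosing an optional prognostic covariate is a preference that a condensed article might leave to a fuller document. The first part stands. The second stands only in part: the article does not leave the comparison open but names the unpaired t-test, so a comment on that choice is fair.

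Three stronger readings are tempting, and the document supports none of them.

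- A reader might infer that the plan has already singled out the pre-randomisation rate as a predictor of decline. It has not. The Spearman sentence fits an on-study rate equally well, so using the baseline rate is a proposal of this review.
- A reader might infer that a chance excess of fast progressors in one arm would bias the result. At 15 per arm, the arm difference in a baseline covariate has a standard error of √(2/15) = 0.37 SD, so sizeable imbalances will occur. But that variability is already in the t-test's standard error, and the test keeps its 5% level. Only precision is at stake.
- A reader might infer that entry is open to any stage of disease. Section 1.2 excludes tracheostomy, invasive ventilation and diaphragmatic pacemakers, which bounds the late respiratory end. Only speed of progression is unrestricted.

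Two limits on the size also stand. No correlation is given, and at r of 0.2 or less adjustment gains nothing or loses slightly. The gains are measured against a model with no covariates; the increment over a model that already holds the baseline value and the bulbar stratum has not been shown and would probably be smaller.

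**Conclusion.** The point holds as a matter of efficiency. Section 1.6 uses an undefined, untimed progression rate only in a correlation, while a usable baseline rate can be derived from planned data and is left out of the comparison of arms. The randomised comparison remains valid and unbiased.

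The expected change in power at 16 per arm runs from a loss of about 1–2 points (r = 0) to a gain of about 9 points (r = 0.5), and becomes material only from about r = 0.3 to 0.4. This rests on an assumed r, on a standardised effect of 1.02 back-solved from the stated sample size, and on no other covariate in the model. It is a cheap improvement, not a correction of an error.

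**What to change.** In section 1.6:

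1. Define the baseline disease progression rate as ALSFRS-R points lost by baseline divided by months from symptom onset to baseline.
2. For each primary decline rate, replace the unpaired t-test by a linear model (ANCOVA) with treatment arm and this rate as one prespecified covariate.
3. Keep the Spearman analysis as descriptive, and state which progression rate it uses and when that rate is measured.
4. State that no progression rate measured after randomisation will be used for adjustment.

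This should be fixed before any comparison by arm is seen, so that looking into baseline imbalances does not lead to choosing covariates afterwards.

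The cost is a few sentences and one model term, with no new data, visit or procedure and no change in sample size. The downside is one degree of freedom, about 1–2 points of power if the rate proves unrelated to decline.

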## Discussion

2

This study will assess the impact of expiratory muscle training associated with breath stacking technique on pulmonary function, respiratory muscle strength, peak cough flow and functional assessment in ALS patients. We chose the pulmonary function parameters and cough efficacy as primary outcomes because they plays a critical role in predicting the prognosis of these patients, both in terms of survival and functional ability [22].

A recent study suggests that expiratory muscle training was feasible and well-tolerated in ALS patients, and led to improvements of expiratory muscle strength and swallowing kinematics [10]. However, no differences were noted for FVC. The breath stacking technique can increase inspired volumes that lead to greater peak cough flow, allowing for improvements in mucus clearance and reduction in atelectasis (6). We believe that the increase of inspired volume may increase the efficacy of expiratory muscle training in the ALS population.

The American Academy of Neurology, Practice Parameters has recommended that breath stacking technique as a respiratory aid in patients with neuromuscular diseases. This trial aims to determine the impact of an inspiratory and expiratory synergist program in ALS patients using the same resuscitation bag with an addiction of a new valve (VUP) that allows for increased lung capacity and the addiction of a submaximal load to expiratory muscles during the expiration phase, which may provide muscular conditioning in ALS patients and contribute to a maintained bulbar function.

## Conclusion

3

ALS patients have a poor survival and demonstrate high burden of disease when their bulbar and respiratory function decline. This randomized trial will assess the effects of home-based program in pulmonary and bulbar function. If beneficial, the intervention is designed in way to enable easy translation into practical guidelines for this population.

